### Questionnaires and scales

The participants will answer the following questionnaires: Dietary Sodium Restriction Questionnaire (DSRQ) [25] for the assessment of sodium-restriction adherence; Self-Care of Hypertension Inventory – Brazilian Version (SC-HI) [26, 27] to measure self-care in hypertension patients; Medication Assessment Questionnaire [MAQ] [28] to evaluate adherence to drug therapy; International Physical Activity Questionnaire (IPAQ) [29] to quantify the level of physical activity; and the Epworth Sleepiness Scale (ESS) [30] to measure daytime sleepiness. All questionnaires will be administered at baseline and at the end of follow-up.

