### Outcomes of interest

The primary outcome of the study will be a reduction of at least 8 mmHg in SBP and changes in DBP and mean BP. These outcomes will be measured by 24-h ABPM at the first and last protocol visits.

Secondary outcomes will include improvement of adherence to a low-sodium diet, adherence to self-care behaviors, regular use of antihypertensive medications, increase or maintenance of physical activity, weight reduction, evaluation of changes in daytime sleepiness, and cessation of smoking. These outcomes will be measured by the aforementioned questionnaires and scales at the first and last protocol visits.

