### Statistical analysis

Continuous variables will be expressed as mean ± standard deviation or median and interquartile range. Categorical variables will be expressed as percentage or proportion. The chi-square test will be used for associations between sociodemographic and clinical variables with SC-HI scores. Student’s t-test or the Mann–Whitney *U* test, depending on data distribution, will be used for between-group comparison of quantitative variables. SBP and DBP measurements obtained during the study, as well as SC-HI scores, will be analyzed by generalized estimating equations with Bonferroni correction. BP differences between groups during treatment will be analyzed by repeated-measures analysis of variance (ANOVA). Analysis of covariance (ANCOVA) will be conducted to adjust possible differences regarding baseline measurements, as well as some risk factors and confounding factors when necessary. The 5% level of significance will be adopted and data will be analyzed in IBM SPSS Statistics for Windows, Version 20.0 (IBM Corp., Armonk, NY, USA).

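### For the quantitative secondary outcomes other than SC-HI, neither baseline adjustment nor the effect measure is fixed in advance, although each is measured at both visits

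*Protocol article*

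**What the plan says.** The Statistical analysis section of the protocol article gives several methods:

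- **Quantitative variables in general:** Student's t-test or the Mann–Whitney test, "depending on data distribution, will be used for between-group comparison of quantitative variables". No criterion for the choice is given, and the text does not say whether final values or changes are compared.
- **SBP, DBP and SC-HI:** the blood-pressure measurements, "as well as SC-HI scores, will be analyzed by generalized estimating equations with Bonferroni correction". Repeated-measures ANOVA is named as well for between-group BP differences.
- **Baseline:** "Analysis of covariance (ANCOVA) will be conducted to adjust possible differences regarding baseline measurements", and the sentence goes on "as well as some risk factors and confounding factors when necessary". No outcome is named for this analysis.

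On data collection, the Questionnaires and scales section states: "All questionnaires will be administered at baseline and at the end of follow-up". Anthropometric measurements says that weight is likewise taken at the first and last visits.

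**The concern.** Once SBP, DBP and SC-HI are set aside, five quantitative secondary outcomes remain: the sodium-restriction score, the medication score, physical activity, sleepiness and weight. The t-test or Mann–Whitney step is the only comparison that clearly applies to them, and two things about it stay open until the data are seen.

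The first is the effect measure. A t-test goes with a mean difference in the outcome's own units. A Mann–Whitney test compares ranks and yields no such difference. Picking between them on the observed distribution lets the data decide what is estimated.

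The second is the use of baseline. The ANCOVA sentence presents adjustment as a remedy for arms that differ at the start. In a randomised trial the better reason is that the baseline value predicts the final value, so including it narrows the confidence interval whether or not the arms happen to differ. Tying adjustment to imbalance makes the use of baseline look conditional on the data.

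At stake are precision that the trial has already paid for and some freedom to choose among analyses after the event. The second matters a little more here because the article's Potential biases section concedes that these outcomes are self-reported and the design is open-label.

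**Working it through.** **The plan's own figure.** The Sample size section gives a difference of 8 mmHg, SD 14 mmHg, 80% power and alpha 0.05.

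- Normal approximation: n per arm = 2 × 14² × (1.960 + 0.842)² / 8² = 48.1, so 49 per arm.
- t-based calculation: 49.05, so 50 per arm. This reproduces the stated 100.

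It is an unadjusted two-sample calculation for SBP. No secondary outcome has a power target, so what follows is illustrative.

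**Inputs for the secondary outcomes**

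- Completers per arm: 60 × (1 − 0.20) = 48, from the Sample size section.
- Effect: d = 0.5 SD of the final value (assumed).
- Baseline-to-final correlation r: not given in the article; assumed to be 0.3, 0.5 or 0.7.
- Equal SD at both visits (assumed); two-sided alpha 0.05.

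**Formulas.** Express each analysis as an effective standardised effect, then take two-sample t-test power at 48 per arm.

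- t-test on final values: d = 0.5, whatever r is.
- t-test on change: the SD of change is SD × √(2(1 − r)), so effective d = 0.5 / √(2(1 − r)).
- ANCOVA with baseline: the residual SD is SD × √(1 − r²), so effective d = 0.5 / √(1 − r²).

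| r | Final-value t-test | Change t-test: d, power | ANCOVA: d, power |
|---|---|---|---|
| 0.3 | 67.9% | 0.423, 53.6% | 0.524, 72.0% |
| 0.5 | 67.9% | 0.500, 67.9% | 0.577, 79.9% |
| 0.7 | 67.9% | 0.645, 87.9% | 0.700, 92.4% |

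ANCOVA is ahead of both alternatives at each of the three correlations. Against change scores its lead falls from 18 points at r = 0.3 to 12 at r = 0.5 and about 5 at r = 0.7. At r = 0.8 the two are 97% and 98%; at r = 0.9 both exceed 99.9%.

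**Does choosing the test from the data inflate type I error?** The article gives no rule, so one was assumed: Shapiro–Wilk in each arm at 5%, then the t-test if both arms pass and Mann–Whitney otherwise. With no true effect, 50 per arm and 6,000 simulated trials per distribution:

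| Distribution | Two-stage type I error | Mann–Whitney chosen | Error if the smaller p-value were reported |
|---|---|---|---|
| Normal | 4.7% | 9.8% | 5.5% |
| Lognormal | 4.8% | 99.5% | 6.6% |
| Exponential | 4.6% | 100% | 7.0% |

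A separate simulation at 48 per arm gave 5.3% for both normal and gamma data. Following such a rule leaves the error rate close to 5%. Even with truly normal data, though, about one trial in ten would switch to the rank test, so chance alone can change the effect measure.

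**The case against.** Four objections deserve an answer.

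**Baseline adjustment is in the plan.** A reader might infer that quantitative outcomes are analysed without any use of baseline. The article does not support that. The ANCOVA sentence is not limited to blood pressure, and its closing condition may qualify only the added risk and confounding factors. This stands, and it narrows the point. On either reading, however, ANCOVA is assigned to no named outcome, is framed as a response to baseline differences, and is not said to replace the t-test.

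**The primary outcomes are not affected.** A reader might extend the point to blood pressure. SBP and DBP are assigned to generalized estimating equations, with repeated-measures ANOVA also named for BP, and SC-HI is assigned to generalized estimating equations. None of these rests on the t-test or Mann–Whitney step alone. This stands in full.

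**The size of the loss depends on things the article does not state.** The 68% belongs only to a t-test on final values. The article words several of these outcomes as change or improvement, and a change-score test does use the baseline value. If weight has a high correlation between visits, which is plausible but assumed, little would be lost. This stands as a limit on size. It does not reverse the direction: ANCOVA remains better over the assumed range.

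**A condensed article leaves detail to the analysis plan.** That is fair for the normality criterion, the covariate list and the handling of skewed scores. The point rests instead on what is printed: a choice of test made from the data, and an adjustment tied to imbalance. Any later plan would have to override that text.

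**Conclusion.** The point holds for the quantitative secondary outcomes other than SC-HI. For these the article leaves the effect measure to the observed distribution and does not commit to baseline adjustment, although the baseline values are collected.

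In the illustration, ANCOVA gains 4, 12 and 24 percentage points of power over a final-value t-test at r = 0.3, 0.5 and 0.7, and 18, 12 and about 5 points over a change-score t-test. These figures rest on an assumed 0.5 SD effect, 48 completers per arm, equal SDs at the two visits and correlations that the article does not give.

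A reader might also conclude that the choice between t-test and Mann–Whitney produces false positives. The simulations do not support that: the two-stage error stayed between 4.6% and 5.3%. Only reporting whichever test gave the smaller p-value would raise it, to 5.5–7.0%, and nothing in the article says this is intended.

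This is an improvement to secondary analyses that costs nothing. It is not a threat to the trial's primary conclusion.

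**What to change.** Replace the general t-test or Mann–Whitney rule, for these outcomes, with one fixed analysis. For each quantitative secondary outcome measured at both visits:

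- fit ANCOVA of the final value on group, with that outcome's own baseline value as covariate, whether or not the arms differ at baseline;
- report the adjusted mean difference with its 95% confidence interval;
- use robust or bootstrap standard errors for skewed scores;
- keep Mann–Whitney as a sensitivity check only.

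The cost is a sentence in the analysis section and no new data. The Trial status section reports 50 patients included and seven completers, so the change can still be made and dated well before the final data exist.

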### Sample size

The sample size was calculated with WinPepi 11.20 software. Delta values of BP levels for the study population as reported by Correa et al. (4.4 mmHg for 24-h SBP and 2.7 mmHg for 24-h DBP) were used [24]. The sample size was estimated at 100 patients, 50 in the IG, and 50 in the CG, considering a difference in SBP of 8 mmHg between groups, a standard deviation of 14 mmHg, 80% power, and alpha = 0.05. To account for 20% attrition, the sample will consist of 120 patients, 60 in each group.

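### The sample size and the analysis section do not agree on the level at which SBP is tested: powered at an uncorrected 5%, analysed both with and without Bonferroni, and no test named as deciding

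*Protocol article*

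**What the plan says.** **Sample size section.** The calculation rests on one comparison of SBP between the groups, "considering a difference in SBP of 8 mmHg between groups, a standard deviation of 14 mmHg, 80% power, and alpha = 0.05". The result is given as "The sample size was estimated at 100 patients, 50 in the IG, and 50 in the CG", followed by "To account for 20% attrition, the sample will consist of 120 patients, 60 in each group". Multiplicity is not mentioned.

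**Outcomes of interest section.** "The primary outcome of the study will be a reduction of at least 8 mmHg in SBP and changes in DBP and mean BP". These are measured by 24-h ABPM at the first and last protocol visits, so there are two time points.

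**Statistical analysis section.** "SBP and DBP measurements obtained during the study, as well as SC-HI scores, will be analyzed by generalized estimating equations with Bonferroni correction". The next two sentences assign between-group BP differences to repeated-measures ANOVA and provide for ANCOVA to adjust for baseline. A preceding sentence gives Student's t-test or Mann-Whitney for between-group comparison of quantitative variables. None of these three carries a correction, and the section closes by adopting a 5% level. It does not say which analysis decides the SBP question, which comparisons the Bonferroni correction covers, or what the divisor is.

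**The concern.** A power statement holds only for the test level it assumes. The Sample size section assumes that SBP is judged at 5%. The sentence in the analysis section that names SBP together with a model attaches Bonferroni to that model, which suggests a stricter level. Other sentences in the same section lead to a test of the same outcome at the full 5%.

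Two things are at stake. First, if the stricter level governs, a true 8 mmHg effect would be missed more often than the planned 20% of the time. Second, whatever the power, the conclusion could depend on which sentence is followed. An uncorrected p-value of 0.03 is positive at 0.05 and negative at 0.05/2 = 0.025.

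**Working it through.** **Inputs.** Difference 8 mmHg ("considering a difference in SBP of 8 mmHg between groups"), SD 14 mmHg ("a standard deviation of 14 mmHg"), 50 evaluable per arm, alpha 0.05 and 80% power, all from the Sample size section. Sidedness is not stated; two-sided is assumed because it reproduces the plan's figure. The Bonferroni divisor m is not stated and is an assumption here: m = 2 (SBP, DBP), m = 3 (SBP, DBP, SC-HI, or the three BP outcomes), m = 6 (all pairs among 2 groups × 2 times: 4 × 3 / 2 = 6).

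**Step 1: reproduce the plan's figure.** Per arm, n = 2 × (z₀.₉₇₅ + z₀.₈₀)² × (SD/difference)² = 2 × (1.960 + 0.842)² × (14/8)² = 2 × 7.85 × 3.0625 = 48.1, so 49. The exact noncentral-t calculation gives 50. A one-sided 5% test would need 38 and does not fit. The 100 evaluable patients are therefore right for an uncorrected two-sided 5%, with no hidden allowance for multiplicity.

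**Step 2: power at a corrected level.** The standardised effect with 50 per arm is 8 / (14 × √(2/50)) = 8 / 2.8 = 2.857. Normal-approximation power is Φ(2.857 − z), where z is the two-sided critical value at 0.05/m. The t columns use the noncentral t for an unadjusted two-sample comparison.

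| m | level | z | power, normal, 50/arm | power, t, 50/arm | power, t, 48/arm | power, t, 60/arm | n/arm for 80% (t) | difference detectable at 80%, 50/arm |
|---|---|---|---|---|---|---|---|---|
| 1 | 0.05 | 1.960 | 81.5% | 80.8% | 79.1% | 87.4% | 50 | 7.9 mmHg |
| 2 | 0.025 | 2.241 | 73.1% | 71.9% | 69.9% | 80.4% | 60 | 8.7 mmHg |
| 3 | 0.0167 | 2.394 | 67.8% | 66.3% | 64.2% | 75.7% | 66 | 9.2 mmHg |
| 6 | 0.0083 | 2.638 | 58.7% | 56.7% | 54.4% | 67.2% | 76 | 9.9 mmHg |

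The 48 per arm is 120 × (1 − 0.20) / 2, the number left after the plan's own attrition; the 60 per arm is no attrition at all. Even with no attrition, 80% is reached only for m = 2.

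**Step 3: allow for baseline adjustment.** The plan does not say whether 14 mmHg is the SD of the follow-up value or of the change. If it is that of the follow-up value, ANCOVA-type adjustment with baseline correlation r reduces it to 14 × √(1 − r²). With an assumed r = 0.5 this is 12.1 mmHg, and power with 50 per arm (normal approximation) is about 91%, 85%, 82% and 75% for m = 1, 2, 3 and 6. Adjustment could thus recover the loss for m = 2 or 3, but not for m = 6 at this correlation.

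**Step 4: set the sentences side by side.**

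| Place | What is tested | Level |
|---|---|---|
| Sample size | between-group SBP difference | 0.05, uncorrected |
| Statistical analysis, GEE sentence | SBP, DBP, SC-HI | Bonferroni, scope and divisor not given |
| Statistical analysis, ANOVA sentence | between-group BP differences | 5%, no correction given |
| Statistical analysis, ANCOVA sentence | baseline-adjusted comparison | 5%, no correction given |

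No row of the analysis section is marked as the one that the sample size refers to.

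**The case against.** The strongest reply is that the plan can be read consistently. The sentence that speaks of BP differences between the groups is the repeated-measures ANOVA sentence. It carries no correction, and the section's 5% level matches the sample size. Bonferroni may apply only to follow-up pairwise comparisons within the GEE, after a single group-by-time test at 5%. On either reading the planned power is intact. This stands, and it rules out the stronger inference that a reader might draw, namely that the stated 80% is not delivered. The documents do not say that the corrected contrast decides.

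A reader might also infer that SBP is being charged for SC-HI, a secondary outcome, while mean BP escapes correction. That is not supported either. SBP, DBP and SC-HI share a sentence because they share a model, and nothing says that alpha is divided across them. The divisors of 2, 3 and 6 are illustrations.

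It can also be said that the Bonferroni family and divisor belong in a statistical analysis plan that is not shown. That is fair for the divisor. It does not answer the point, because the article itself states an uncorrected alpha, a corrected analysis and uncorrected analyses of one outcome, and does not rank them. Finally, the unadjusted figures may overstate the loss, as Step 3 shows. That is conditional on what the 14 mmHg describes and on a correlation the document does not give.

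**Conclusion.** The point holds as a disagreement over the test level for SBP, not as a demonstrated loss of power. The sample size is correct for an uncorrected two-sided 5%. The analysis section offers both a Bonferroni-corrected GEE and uncorrected tests at 5%, with no order of precedence.

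- If the corrected GEE contrast decides, power for 8 mmHg is about 72%, 66% or 57% for m = 2, 3 or 6, so the chance of missing that effect rises from 19% to between 28% and 43%. This assumes SD 14, 50 per arm, an unadjusted two-sided comparison, and a divisor that the document does not give.
- If the uncorrected ANOVA or a GEE group-by-time test at 5% decides, the stated power stands, provided 14 mmHg is the SD of the quantity that test compares.

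The ambiguity matters on either branch, because a result between the two levels could be declared positive or negative after the data are seen.

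**What to change.** In the Statistical analysis section:

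1. Name one primary test: the single between-group contrast in 24-h SBP at six months, adjusted for baseline, from one named model, at two-sided 5% without Bonferroni. This is the level that the Sample size section assumes.
2. Test DBP and mean BP only if SBP is significant, with Bonferroni between the two or in a fixed order. The gate is needed: SBP at 5% plus DBP and mean BP at 2.5% each, without it, allows a familywise error of up to 0.05 + 0.025 + 0.025 = 0.10.
3. Report SC-HI and the remaining pairwise GEE contrasts as secondary.

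If the sponsor prefers to keep the SBP contrast under Bonferroni, state the divisor and the comparisons it covers, and restate the power in the Sample size section at that level.

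The cost is a few sentences, or a less favourable power figure. No extra patients or data are needed. The Trial status section reports 50 patients included and seven completed, so when the article was written the change could still be made well before the final analysis.

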### Study protocol

Patients will be identified by the HCPA hypertension clinic appointment schedule and invited to participate in the study. The first appointment will serve to obtain informed consent and confirm eligibility. Then, the patient will be randomized to either IG or CG. Participants of both groups will attend a total of six monthly appointments, scheduled by prearrangement, at the HCPA Clinical Research Center. At the first and last protocol visits, the clinical and sociodemographic questionnaire and the other study instruments will be applied, anthropometric measurements will be obtained, and the 24-h ABPM device will be placed. Each appointment will have an average duration of 30 min. Patients will be reminded of consultations the day before via phone calls; missed appointments will be rescheduled. Appointments should take place within a one-week interval of the 30-day time point since the preceding visit. The primary outcome of the study will be a reduction of at least 8 mmHg in SBP and changes in DBP and mean BP, all assessed by 24-h ABPM. The secondary outcomes will include improvement of adherence to a low-sodium diet, adherence to self-care behaviors, regular use of antihypertensive medications, improvement or maintenance of levels of physical activity, changes in daytime sleepiness, weight loss, and cessation of smoking. These outcomes will be assessed by appropriate questionnaires (described in detail below); weight loss will be measured directly during visits and cessation of smoking will be self-reported. Analysis will follow the intention-to-treat principle. All collected data will be stored in Microsoft Excel spreadsheets and tabulated by the double data entry method. The results of the trial will be communicated to the participants in a meeting organized at the end of the study.

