### Twenty-four-hour ambulatory blood pressure monitoring

ABPM will be conducted with periodically calibrated devices (DINAMAPA-2000, Cardio Systems Coml. Indl. Ltda.), with cuff size selected in accordance with the patient’s arm circumference. The protocol includes BP measurements every 15 min during the daytime (06:00 to 22:00) and every 30 min during the nighttime (22:00 to 06:00). ABPM will be considered satisfactory if at least 16 valid readings during the daytime and eight valid readings during the nighttime are obtained [18]. Participants will be evaluated by ABPM at the baseline and at the end of the follow-up (six months) in order to register BP during both sleep and wakefulness.

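### Ambulatory blood pressure is given to GEE, repeated-measures ANOVA and a conditionally worded ANCOVA with none named primary; one baseline-adjusted ANCOVA should be fixed in advance

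*Protocol article*

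**What the plan says.** All statements are in the protocol article. Its Statistical analysis section names blood pressure in two separate sentences. The first reads: "SBP and DBP measurements obtained during the study, as well as SC-HI scores, will be analyzed by generalized estimating equations with Bonferroni correction". The next reads: "BP differences between groups during treatment will be analyzed by repeated-measures analysis of variance (ANOVA". ANCOVA follows, which "will be conducted to adjust possible differences regarding baseline measurements, as well as some risk factors and confounding factors when necessary". The covariates other than baseline are not named. On error rate the section says "The 5% level of significance will be adopted". It does not rank the methods or say which one decides the trial. A general rule (t-test or Mann-Whitney, by distribution) covers quantitative variables without naming BP.

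The section on ambulatory monitoring fixes the data: "Participants will be evaluated by ABPM at the baseline and at the end of the follow-up". There is one reading before and one after the intervention.

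The Sample size section plans for an 8 mmHg difference in SBP with "a standard deviation of 14 mmHg, 80% power, and alpha = 0.05". That is a plain comparison of two means, and the article ties it to none of the methods above.

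**The concern.** The protocol assigns competing analyses to its own primary outcome. That is a feature of what is written, not a detail left to an analysis plan.

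With only two readings per patient the methods are not interchangeable. The group-by-time term of the ANOVA is the t-test on change. Its group main effect averages the pre-treatment reading with the final one, so a true effect of 8 mmHg appears as 4. ANCOVA compares final values given baseline and is the more precise estimator. Two analysts following the same section could report different p-values for the same trial.

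The ANCOVA sentence can also be read as making baseline adjustment depend on whether an imbalance is seen. On that reading the precision offered by the baseline ABPM, already collected in every patient, is used only sometimes. On either reading the set of further covariates is open.

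**Working it through.** **Inputs from the protocol article.** Difference 8 mmHg, SD 14 mmHg, alpha 0.05 (sidedness not stated; two-sided reproduces the plan), 80% power, 50 per arm before attrition, 60 per arm enrolled, 20% attrition, ABPM at two time points.

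**Assumptions.** The baseline-to-final correlation r is not given, so 0.3, 0.5 and 0.7 are used. The article does not say whether SD 14 belongs to the final value or to the change. It is first taken as that of the final value, with the same SD at baseline.

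**1. The plan's own figure.** n per arm = 2 × (1.960 + 0.842)² × 14² / 8² = 48.1, so 49 per arm, or 98 in all. With the t distribution it is 50 per arm, or 100, with power 0.81. The stated 100 is reproduced. After 20% attrition, 60 × 0.8 = 48 per arm remain, and the two-mean t-test then has power 0.79.

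**2. Standard deviation under each method.**
- Change score (ANOVA interaction): 14 × √(2(1 − r)) = 16.57 / 14.00 / 10.84.
- ANCOVA: 14 × √(1 − r²) = 13.36 / 12.12 / 10.00.
- ANOVA group main effect, i.e. the patient's mean of two readings: 14 × √((1 + r)/2) = 11.29 / 12.12 / 12.91, with effect (0 + 8)/2 = 4.

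**3. Power at 48 per arm** (two-sided 5%, noncentral t).

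| Method | r = 0.3 | r = 0.5 | r = 0.7 |
|---|---|---|---|
| ANCOVA | 0.83 | 0.89 | 0.97 |
| Change score / ANOVA interaction | 0.65 | 0.79 | 0.95 |
| ANOVA group main effect | 0.41 | 0.36 | 0.32 |

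The variance of ANCOVA relative to the change score is (1 − r²)/(2(1 − r)) = (1 + r)/2 = 0.65 / 0.75 / 0.85.

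**4. If SD 14 is that of the change.** The change score has power 0.79 at every r, and ANCOVA has 0.93 / 0.89 / 0.85. ANCOVA is still ahead throughout.

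**5. Type I error if the choice followed the results.** Simulation with normal data, no effect, 48 per arm, r from 0.3 to 0.7, SBP alone:
- better of change score and ANCOVA: about 6.7-8%;
- the same, with the ANOVA main effect also counted: about 11%.

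**6. Type I error if ANCOVA is used only after a significant baseline difference** (p < 0.05), with an unadjusted test otherwise: between 0.034 and 0.051 in simulations at 48 and 50 per arm. This does not exceed 5% beyond simulation error.

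**7. After the fix.** A single ANCOVA fixed in advance has simulated type I error of about 5%.

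**The case against.** The strongest reply is that the menu is shorter than it looks. With two readings and complete pairs, the ANOVA interaction is the change-score test, and a GEE group-by-time term addresses the same contrast. The outcomes are worded as reductions and changes, which points to the interaction and not the main effect. GEE also carries a Bonferroni correction, so it is not simply another test at 5%. Naming any one of the stated methods would close the gap. Most of this stands. It is why the error figures above use only the change score, ANCOVA and, separately, the main effect, and why the low main-effect power is the cost of one possible reading and not of the plan as a whole. It does not remove the choice between change score and ANCOVA.

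The closing qualifier of the ANCOVA sentence may govern only the risk and confounding factors, which would leave baseline adjustment unconditional. That reading is possible. The sentence should then say so, and the covariates would still be unnamed.

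Some stronger readings are tempting but not supported:

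- **That the ANOVA contradicts intention-to-treat.** The article says "Analysis will follow the intention-to-treat principle" and no more. Analysing patients in their allocated arm by ANOVA is compatible with that. Without imputation, ANOVA loses patients who have no final ABPM, but so do a change-score test and a plain ANCOVA. Rules for missing readings may sit in documents not shown.
- **That adjusting on observed imbalance makes the p-value invalid.** Step 6 shows no inflation. The loss is in precision.
- **That the t-test or Mann-Whitney is a further BP analysis.** The sentence does not name BP and may concern baseline or secondary variables.
- **That testing SBP, DBP and mean BP belongs in the same error figure.** That is a separate multiplicity question, and its size depends on correlations that the article does not give.

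**Conclusion.** The point holds in this form: the decisive BP analysis is left open between GEE, repeated-measures ANOVA and ANCOVA, and the ANCOVA wording leaves baseline adjustment ambiguous and its other covariates unspecified. Nothing in the article says the test will be picked after seeing results. The present wording does not exclude it, and the cost would then be a type I error of about 6.7-8% on SBP, or about 11% if the ANOVA main effect were among the candidates.

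The firmer loss is power. At 48 per arm, with SD 14 as the final-value SD, ANCOVA gains about 18, 10 and 3 percentage points over the change score at r = 0.3, 0.5 and 0.7. With SD 14 as the SD of change, the gain is about 14, 10 and 6 points. The exact gain depends on the assumed correlation, but ANCOVA is ahead at every value tried. The planned sample is large enough for it: power exceeds 0.80 at 48 per arm in all these cases.

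**What to change.** In the Statistical analysis section, replace the BP sentences with one primary analysis: ANCOVA of six-month 24-h SBP on arm and baseline 24-h SBP, carried out in every case, at the two-sided 5% level, reported as an adjusted mean difference with a 95% confidence interval. Remove the conditional qualifier, and name any further covariates before outcomes are examined. Use the same model for DBP and mean BP. Keep GEE and repeated-measures ANOVA only as labelled sensitivity analyses, and state that the ANOVA result is the group-by-time term.

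Optionally, fit the primary analysis as a mixed model on both readings with the baseline means constrained equal across arms. It estimates the same contrast and keeps patients who have no final ABPM.

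The cost is wording only: no new patients, visits or measurements. The Trial status section reports 50 patients included and seven completed at the time of writing, so at that point the choice could still be fixed before most outcome data existed. If more data have since accrued, it should be made without sight of outcomes by arm, and dated.
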